## Discussion

Why publish a study protocol? This study aims to show that pelvic physiotherapy in combination with standard medical care is more effective than standard medical care alone in constipated children. To our knowledge, this article is the first to describe the design of an RCT among children with FC to assess the effect of PPT as an add-on to SMC. The Dutch Pelvic Physiotherapy Protocol (DPPP) presented here is based on the available literature, a survey and a Delphi procedure among experts. Exchanging knowledge and expertise with other researchers is important in order to prevent duplicate research. Consequently, it has been decided to publish the study protocol prior to achieving results.

The DPPP was developed between 2007 and 2009. Given that no studies have so far been published on the effect of PPT in childhood constipation [52] and that a repeat survey on standard PPT among 49 Dutch physiotherapists in 2011 did not yield substantial differences compared to the 2007 survey, we feel this protocol is as up-to-date as possible.

In the absence of an evaluation tool, we will use parameters for male adults to define the proper childhood pelvic floor muscle functions. These values are expected to be similar to the children’s, as is also the opinion of the experts and the literature [36].

Confounding in our trial may arise due to the Hawthorne-effect as a result of differences in number of the protocolised contacts. Although it is expected, based on experience, that the mean number of treatment sessions will be equal, adjusted group differences will be analysed.

Biofeedback, as a modality of PPT, is an umbrella term in the literature, covering different types of treatment, e.g. manometry (MT), myofeedback (electromyography feedback) (MFB), rectal balloon training (RBT), functional electric stimulation, flowmetry and ultrasound scan. It is administered in various ways depending on availability, costs, setting (clinic/private, discipline involved [physiotherapist/nurse/medical doctor]) and country. There are also differences in the biofeedback method used (peri-anal surface electrodes, intra-anal probes, anal manometry or RBT), the practitioner administering it (gastroenterologist, paediatrician or psychologist), number of treatments and outcome [53-58]. Furthermore, trials show a substantial lack of quality and harmonisation, resulting in heterogeneous treatment protocols and difficulties when interpreting the findings reported in the literature. Mixed results of BF treatment for constipation have been reported [24,54,57,59,60].

FC caused by pelvic floor dysfunction or delayed colonic transit can manifest itself as a single or combined problem [61]. The behavioural approach, concentrating on toilet training and learning to recognise signals from the body such as the urge to defecate, is important for all constipated children [18]. To date, the relationship between pelvic floor muscles, breathing, trunk control and posture [21,22,25,26] has been largely ignored. Therefore, we feel that PFM training must be included in the treatment and should be the starting point of the therapy, rather than being studied as a single modality.

In order to standardise pelvic physiotherapy and minimise information bias, the treatment protocol has been designed in consultation with all participating specialised physiotherapists, who are experienced in treating constipated children.

As with most physiotherapeutic and medical interventions, the practitioner and patient will not be blinded to the treatment interventions. However, the investigator and patient will be blinded for the web-based and PPT baseline measurements and diary data.

Potential confounders will be the presence of urinary incontinence, enuresis, abdominal pain and the use of laxatives [1,18,47]. The presence of incontinence, enuresis and pain can influence the perception of patients' quality of life or may distort the SDQ and GPE scores.

Patients' compliance with the home toilet training and the use of laxatives will be monitored, as it determines the therapy intensity and, indirectly, the success of the therapy. Finally, the use of laxatives will be taken into account, as it can influence the number of stool events and consistency. The results of this trial will be used to evaluate the proposed Dutch pelvic physiotherapy protocol and to determine normal values for the pelvic floor muscle function in children. These outcomes will serve as recommendations in the guideline on PPT in constipated children, which will be developed using the standard method for clinical practice guideline development of the Royal Dutch Society for Physical Therapy (KNGF).

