## Methods/design

### Trial design, hypothesis and research

To date, there has been little scientific evidence evaluating the effectiveness of pelvic physiotherapy (PPT) in childhood constipation [7,14,29,30]. Therefore we designed a two-armed multicentre randomised controlled clinical trial (RCT). We hypothesise that the combination of standard medical care (SMC) and PPT will prove more effective than SMC alone for the treatment of FC in children aged 5 to 17 years.

Secondary research questions are: (1) Does PPT add to the child’s quality of life, as defined by the strengths and difficulties questionnaire (SDQ), the numeric rating scale (NRS) in relation to the perceived severity of the problem and the global perceived effect (GPE), (2) what values of the pelvic floor muscle function (PFMF) in children can be defined based on the results of the study in clinically relevant subgroups, according to the international continence society (ICS) criteria.

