### Participants

#### Study population

Children living in the Netherlands and referred to pelvic physiotherapy by paediatricians from various hospitals will be enrolled in this study.

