#### Inclusion criteria

(1) age 5–17 years, (2) functional constipation according to the Rome III criteria, (3) attending regular schools, (4) parent(s) sign(s) an informed consent, (5) children aged over 11 years sign an informed consent themselves, and (6) the child and parent(s) are motivated to participate in the study.

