#### Secondary outcome measures

Numeric rating scale

The two single-item 1–10 numeric rating scales (NRS) measure perceived severity of the problem by the parents and estimate the child’s experience [37].

Strength and Difficulties Questionnaire (SDQ).

The validated SDQ has two versions, one for parents (7–19 years) and one for children (11 years and over), which were developed using the ‘diagnostic and static manual of mental disorders classification’ for psychosocial problems, as these problems (anxiety, depression, behavioural disorders and attention deficit hyperactivity disorders) are relatively common among young people. The total score ranges from 0 to 40 points, with established cut-off points at 0–10 (normal), 11–13 (borderline, presence of less serious issues) and above 14 (high) [38-40].

Global perceived effect

The global perceived effect (GPE) instrument is a subjective score that simply shows the perceived change in symptoms during and after treatment, ranging from 1 (much worse) to 9 (complaints have disappeared). The GPE will be administered at MT-WB 2 and MT-WB 3 before the final visit to the physiotherapist.

Pelvic floor muscle function

The following measurements will be done by the physiotherapist at the second (MT-PPT 1) and final visit (MT-PPT 2).

• Digital testing

• Digital testing will be used to measure the ability and reflex action of the pelvic floor muscles (PFM) at rest and during contraction, cough and straining to defecate. The tone of the internal and external anal sphincters and puborectalis muscle will be palpated, and the sensitivity, anal reflex and presence of stool evaluated. Strength, endurance, coordination and the ability to close the rectum will be evaluated by asking the child to contract and relax the PFM, and then to hold the contraction for 30 seconds. At the same time, the pelvic physiotherapist will assess whether the child is contracting the extra-pelvic muscles, like the abdominal, gluteal and adductor muscles.

• Myofeedback

• Myofeedback uses the electromyographic (EMG) signal of the pelvic floor muscles. The level of the EMG signal should increase while contracting, whereas the signal should decrease at relaxation [15,17,41,42]. Given the absence of an assessment instrument to define proper muscle tone of children's pelvic floor, parameters for the male adults will be used [28,29,36,43].

• For the purpose of this study, the small intra-anal PelviRing Anal Probe will be used.

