### Data analysis

After checking for missing data and testing for normality, group differences will be analysed using the Pearson Chi-square test, or likelihood ratio in the case of dichotomous outcomes. Continuous outcomes will be analysed using the independent samples t-test or the Mann–Whitney U test. Adjusted group differences will be analysed using multivariable logistic regression with ordinal variables transformed into dummies, taking into account possible differences in mean number of sessions. Finally, subgroup analyses will be done to establish normal values and observed differences in effectiveness for relevant clinical subgroups.

Data analysis will be done according to the intention-to-treat principle. Characteristics of the study population at baseline will be described. Potential effect modifiers like age and gender [10,14], as well as potential confounders like urinary incontinence, enuresis and abdominal pain will be taken into account [17,47-51]. To assess selection bias, responders and nonresponders will be compared in terms of relevant clinical and demographic variables. Data analysis will be carried out using SPSS version 19.0 (SPSS Inc., Chicago, Illinois). A two-tailed p-value of 0.05 will be considered statistically significant.

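### The plan says it will establish normal pelvic-floor values in children, but every enrolled child is a referred patient with functional constipation, so it can only describe patient values

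*Protocol article*

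**What the plan says.** Two places in the protocol article state the aim. Under Data analysis, "subgroup analyses will be done to establish normal values and observed differences in effectiveness for relevant clinical subgroups". Near the end of the Discussion, the results are to be used "to determine normal values for the pelvic floor muscle function in children", and the outcomes are to become recommendations in a guideline on pelvic physiotherapy for constipated children.

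The sample is fixed elsewhere. The second inclusion criterion is "functional constipation according to the Rome III criteria". Under Study population: "Children living in the Netherlands and referred to pelvic physiotherapy by paediatricians from various hospitals will be enrolled in this study". Framework of the study sets up two arms, standard medical care alone and standard medical care plus pelvic physiotherapy, both drawn from these children.

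Two further places bear on the point. The Background calls dyssynergic pelvic-floor dysfunction the major reason for FC in children. For judging muscle tone, Secondary outcome measures says that, for want of a paediatric instrument, "parameters for the male adults will be used".

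**The concern.** A normal or reference value describes people without the disorder in question. Here nobody enters without it, and the measured function is the one the protocol itself links to the disorder. The control group does not help: it is a control for treatment, made up of constipated children on standard care.

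At stake is what the trial may conclude on a secondary aim. Followed as written, the plan would put patient measurements into a guideline under the label of normal values. Practitioners would then judge constipated children against limits that were themselves taken from constipated children. A larger sample would narrow the uncertainty around those limits without changing whom they describe.

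**Working it through.** No figure in the plan decides this point, so the check sets the aim beside the design.

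1. **Aim.** Normal values in children, with no restriction to patients (Discussion), obtained from subgroup analyses within the trial (Data analysis).
2. **Who is measured at baseline.** FC is required (Inclusion criteria) and every child is a referral (Study population). The share with FC at the first physiotherapy measurement is 100%, so the number of non-constipated reference children is 0.
3. **Whether another source of norms is described.** None is. Both arms are patients (Framework of the study). The normality standard in use is taken from adult men (Secondary outcome measures), and the Discussion expects children's values to be similar. Without unaffected children the trial cannot test that expectation.
4. **Whether children recovered at six months could serve.** Inputs from Power of the study: 367 enrolled, 20% drop-out, success of 60% with standard care and 75% with added physiotherapy. Randomisation is 1:1, and drop-out is assumed equal in both arms.
   - Measured at six months: 367 × 0.80 = 293.6, or 146.8 per arm.
   - FC absent: 146.8 × 0.60 + 146.8 × 0.75 = 88.1 + 110.1 = 198.2.
   - FC still present: 293.6 − 198.2 = 95.4.

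   About 198 children would thus be free of FC, of whom about 110 (110.1 / 198.2 = 56%) would have had the pelvic-floor training. All are treated former patients selected on outcome. The primary outcome definition also allows them to be taking less than 10 g of macrogol a day. They can be described as recovered patients, but they are not a sample of unaffected children. The document does not say that the normal values would come from this group.

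On every route the design offers, the values obtained belong to current or former patients.

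**The case against.** **The secondary research question is worded more carefully.** It asks "what values of the pelvic floor muscle function (PFMF) in children can be defined based on the results of the study in clinically relevant subgroups", refers to International Continence Society criteria, and does not use the word normal. This stands: that sentence needs no change. It does not cover Data analysis and the Discussion, which do use the word.

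**Some patients may have a sound pelvic floor.** The Background puts the abnormal defecation pattern at about 50% of children, and the Discussion allows that delayed transit can be a problem on its own. The exclusion of neurological, endocrine and surgical disease also brings the sample nearer to the general population. A subgroup without pelvic-floor dysfunction is therefore conceivable. It would still be a referred, constipated group, so it would not give population norms.

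**The reach is limited.** The guideline is for constipated children, not for all children. This narrows the consequence. It does not make patient values normal.

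A reader might also infer more than the documents support:

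- *That a central 95% range would label most dysfunction as normal.* No such range is specified, and the 50% refers to a defecation pattern that is not mapped to the myofeedback or balloon measurements.
- *That the limits would be shifted toward dysfunction.* Resting tone counts as abnormal both above 5 μV and below 2 μV, so a patient sample could move or widen the limits either way.
- *That the exercise is circular because of the adult-male cut-offs.* It would be so only if those cut-offs selected the children called normal, and the plan does not say that they do.

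**Conclusion.** The point holds as a mismatch between a stated aim and the enrolled population. Data analysis and the Discussion promise normal values, and the design can deliver only values in children with FC before treatment and in treated children afterwards. The conclusion rests on the stated eligibility criteria and on the absence of any described non-constipated group. It needs no assumption about how the limits would be calculated. The shortfall is complete at baseline, with zero reference children. The size and direction of the bias in any resulting limits cannot be derived from the document.

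The effect is confined to this secondary aim and its later use in the guideline. The primary outcome, the sample size and the comparison between arms are untouched.

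**What to change.** In Data analysis and in the closing part of the Discussion, replace the aim of establishing or determining normal values with this: to describe the distribution of pelvic-floor measurements in children with FC at baseline, by clinical subgroup, and their change by arm. Add one sentence saying that these are patient values and will not be offered to the guideline as norms.

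The cost is wording only. No visit, measurement or sample-size change follows. The sponsor gives up a claim that the data cannot support. Keeping that claim would require a non-constipated reference sample, which the trial does not have.

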## Endnote

The web-based medical software had been developed by Fastguide, Bergen op Zoom, the Netherlands.

## Abbreviations

BF: Biofeedback; DPPP: Dutch pelvic physiotherapy protocol; EMG: Electromyography; FC: Functional constipation; GPE: Global perceived effect; ICS: International continence society; KNGF: Royal Dutch Society for Physical Therapy; NRS: Numeric rating scale; M-WB: Measurement, web-based; M-PPT: Measurement at PPT practice; MFB: Myofeedback; PFM: Pelvic floor muscles; PFMT: Pelvic floor muscle training; PPT: Pelvic physiotherapy; RBT: Rectal balloon training; RCT: Randomised controlled trial; SDQ: Strengths and Difficulties Questionnaire; SMC: Standard medical care.
